### Experimental design

This study is designed as a three-arm randomized controlled trial. Given the limited number of longitudinal studies examining exercise interventions in esports, our sample size estimation was informed by the results of existing acute or short-term exercise studies aimed at enhancing esports performance, alongside preliminary data from our previous research [27,35]. Based on the effects of exercise on esports performance reported in these studies, we conservatively estimated a moderate effect size (d = 0.4) to power our primary outcomes (esports performance). Power analysis conducted via G*Power indicated that a minimum sample of 52 participants per group would be required to detect significant effects with 80% power (α = 0.05). Accounting for an anticipated dropout rate of 20%, 65 participants for each group will be recruited for this study. In total, we will recruit 195 participants, and they will be randomly allocated into three groups (1:1:1): HIIT, MICT, and a control group. To prevent baseline imbalances in variables relevant to gaming performance, a stratified block randomization procedure will be employed. Participants will be stratified into two strata based on their years of FPS gaming experience (e.g., above vs. below the median years of experience of the recruited cohort). Within each stratum, participants will be randomly allocated to the HIIT, MICT, or control group in a 1:1:1 ratio using randomly permuted blocks. The randomization sequence will be generated by an independent researcher using a computer-based random number generator (Research Randomizer) to ensure allocation concealment. The entire allocation process will be conducted by a staff member who will not be participating in the study. In scenarios requiring assessors to utilize measurement tools for evaluating metrics, we engage testers who are completely blind to the participants’ group assignments to conduct the assessments. For metrics tested via computer, our assessors serve merely to facilitate and oversee the process, with the computer’s saved data serving as the definitive record to ensure data objectivity. This approach has been proven reasonable in the past esports performance assessment [27]. The intervention groups will receive a 12-week HIIT or MICT exercise program, while the control group will not receive any intervention. All groups will report their dietary intake, physical activity, sleep patterns, and gaming activity. All participants will undergo a baseline test, followed by an immediate post-test at the end of the 12-week intervention period and a follow-up test 4 weeks after the intervention ends. Fig 2 illustrates the specific experimental procedure.

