The primary outcome will be tested at a two-sided α level of 0.05. For the secondary outcomes, the resulting *p*-values for the group-by-time interaction effects derived from the GEE models will be adjusted using the Benjamini-Hochberg False Discovery Rate (FDR) method. If significant main or interaction effects are detected in the GEE model, simple effect analyses and post-hoc pairwise comparisons will be performed within the GEE framework using estimated marginal means with a Bonferroni adjustment.

Prior to investigating potential associations, we will first test for true inter-individual differences in response to the intervention by comparing the variance of the change between the groups [99]. If true inter-individual variability is confirmed, Pearson’s or Spearman’s rank correlation coefficients will be utilized, as appropriate, to investigate potential associations between esports performance indicators and hand correlates, body composition, and physical competence. To account for multiple testing in these correlation analyses, p-values will be adjusted using the Benjamini-Hochberg FDR method.

All statistical analyses will be conducted using R software (version 4.4.2). A two-sided *p*-value of < 0.05 will be considered statistically significant. To indicate the precision of the estimates, 95% confidence intervals (CIs) will also be calculated and reported.

For the exploratory qualitative component, all semi-structured interviews will be audio-recorded and transcribed verbatim. The transcripts will be analyzed using thematic analysis, facilitated by NVivo 12 software, to identify, analyze, and report recurring themes within the participants’ subjective experiences. Although the sample size is fixed by the intervention design, we will continuously monitor for thematic saturation during this data analysis phase. Rather than formally merging these findings with the quantitative data in a mixed-methods matrix, the qualitative themes will be utilized during the interpretation phase to contextualize the objective performance outcomes. This approach will provide a deeper understanding of the participants’ perspectives and assist in elucidating the potential underlying mechanisms between aerobic exercise and esports performance.

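### Bonferroni for the three pairwise arm comparisons of flicking capacity is valid but needlessly conservative; a step-down rule keeps the same 5% familywise error with more power

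*Protocol article*

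**What the plan says.** Under Experimental design, participants are "randomly allocated into three groups (1:1:1): HIIT, MICT, and a control group". The sizing assumption is "we conservatively estimated a moderate effect size (d = 0.4) to power our primary outcomes (esports performance"), and the result is "a minimum sample of 52 participants per group would be required to detect significant effects with 80% power (α = 0.05"). Attrition is then added: "Accounting for an anticipated dropout rate of 20%, 65 participants for each group will be recruited for this study".

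Under Data analysis, "The primary outcome will be tested at a two-sided α level of 0.05", with the GEE group-by-time interaction as the effect of interest. Pairwise testing is conditional: "If significant main or interaction effects are detected in the GEE model", simple-effect analyses follow and "post-hoc pairwise comparisons will be performed within the GEE framework using estimated marginal means with a Bonferroni adjustment". The number of comparisons in the Bonferroni family is not given. Outcomes are measured at baseline, week 12 and week 16, so the interaction has (3 - 1) × (3 - 1) = 4 degrees of freedom.

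**The concern.** A significant interaction says only that the arms do not all change alike. The objectives ask which mode works and whether the two modes differ, and those answers come from the pairwise step. If Bonferroni covers the three pairs at a visit, each pair is judged at 0.05/3 = 0.0167.

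With exactly three arms that penalty is larger than it needs to be, because the three null hypotheses are logically linked. At a fixed sample size, real effects of exercise on flicking would be missed more often than a 5% familywise rule requires.

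**Working it through.** **The plan's own figure.** The test behind 52 per group is not named. A paired or one-sample t test with d = 0.4, two-sided 0.05 and 80% power needs 51.01, hence 52. Then 52/0.80 = 65, as stated. A two-group comparison with the same inputs needs 99 to 100 per arm. That sizing question is separate; here 52 and 65 per arm are taken as given.

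**Assumptions.** Unit SD on the analysed scale; d = 0.4 in both exercise arms unless stated; a Bonferroni family of three pairs at one visit; normal approximation; pairwise testing already opened by the gate.

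**One contrast, by formula.** Power = Φ(d/√(2/n) - z), with z = 1.960 at 0.05 and 2.394 at 0.0167.
- n = 52: 0.4/√(2/52) = 2.040. At 0.05, Φ(0.080) = 53%. At 0.0167, Φ(-0.354) = 36%.
- n = 65: 0.4/√(2/65) = 2.280. At 0.05, Φ(0.320) = 63%. At 0.0167, Φ(-0.114) = 45.5%.

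**Why a step-down rule is valid.** The nulls are HIIT = control, MICT = control and HIIT = MICT. If any two hold, so does the third, so the number of true nulls is three, one or none.
- Three true: a false rejection requires the smallest p-value to fall below 0.05/3, which has probability at most 3 × 0.05/3 = 0.05.
- One true: it can be rejected only if its own p-value is below 0.05.

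Shaffer's rule therefore holds 5% at one visit. A gate in front of it can only remove rejections, so this is true whatever the gate is.

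**Power at week 12** (400,000 simulated trials per row and sample size):

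| Rule, gate open | HIIT vs control, n = 52 / 65 | Both exercise arms vs control, n = 52 / 65 |
|---|---|---|
| Bonferroni | 36.1% / 45.5% | 20.5% / 28.9% |
| Holm | 38.6% / 48.4% | 25.4% / 34.6% |
| Shaffer | 42.5% / 52.8% | 33.3% / 43.4% |
| 2-df week-12 test at 0.05, then pairs at 0.05 | 45.2% / 55.6% | 35.7% / 46.0% |

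The last row replaces the plan's gate by its own 2-df test.

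**Unequal effects (HIIT 0.4, MICT 0.2).** HIIT against control goes from 36.2% (Bonferroni) to 38.4% (Shaffer) and 40.7% (2-df test then pairs) at 52 per arm. At 65 the figures are 45.3%, 47.6% and 49.8%. The gains are about 2 and 4.5 points.

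**Familywise error at week 12 (n = 52).**
- All arms equal: Bonferroni 4.4%, Shaffer 4.4%, 2-df test then pairs 5.0%.
- One arm different by 0.4: 1.7%, 4.3% and 4.6%.
- One arm different by 1.5: 1.7%, 5.0% and 5.0%.

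**Role of the gate.** If the gate were the 4-df interaction alone (assumed correlation 0.6 between weeks 12 and 16), gate plus Bonferroni would give 32% and 42% for HIIT against control. The 2-df rule then gains 13 to 14 points, or about 11 with unequal effects.

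**The case against.** Bonferroni after an overall test is standard, prespecified and valid. The article tests the primary outcome at 0.05 through the interaction and calls the pairs post-hoc. It does not promise each pair at 0.05, and it does not say which test gave 52. A reader might infer that the sizing and the analysis contradict each other on alpha; the text does not go that far. This objection stands, and it limits the point to efficiency.

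A reader might also infer a loss of 13 to 15 points per contrast. That figure treats the gate as the 4-df interaction and credits the change of gate to the adjustment. The article opens pairwise testing on any significant main or interaction effect, so a practice gain shared by all arms could open it through the time effect. Under an assumed 0.3 SD practice gain it opened in 98% of simulated trials. Against an open gate, the 2-df rule gains about 9 to 10 points with equal effects and 4.5 with unequal ones.

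The third tempting reading is that Bonferroni adds no error control and can be deleted. It cannot, with the gate as written. With that practice gain and an assumed within-person correlation of 0.5, unadjusted pairs gave a familywise error of 12% at week 12 and 21% over weeks 12 and 16. Bonferroni over three pairs gave 4.3% and 8.0%. The closed-test argument also covers one visit only: using the 2-df rule separately at both visits gave 8.8% overall when all arms are equal.

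What the objection does not answer is that a step-down rule keeps an adjustment, holds 5% at week 12 under the same gate, and never rejects less than Bonferroni.

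**Conclusion.** The point holds as a minor efficiency improvement. For three arms at one visit, Shaffer's step-down rejects everything Bonferroni rejects at the same 5% familywise limit. With d = 0.4 in both exercise arms and an open gate, it adds 6 to 7 points per exercise-control contrast and about 13 to 15 points for showing both. Holm adds 2 to 3 points per contrast. With effects of 0.4 and 0.2, Shaffer adds about 2.

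These sizes rest on a Bonferroni family of three and on d = 0.4 applying between arms on the analysed scale. The article states neither. The validity argument depends on neither. Type I error control at week 12 is not at fault in the current text.

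**What to change.** For the primary outcome at week 12, replace the Bonferroni wording under Data analysis by Shaffer step-down p-values over the three pairs: smallest at 0.05/3, then the remaining two at 0.05. Holm is a simpler but weaker choice.

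Alternatively, narrow the gate for this outcome to the 2-df group difference in change at week 12, tested at two-sided 0.05, and then test each pair at 0.05. A practice gain common to all arms cancels from that test. Compared with Bonferroni and an open gate, this gains about 4 to 10 points per contrast.

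Either way, do not remove the adjustment while the broad main-or-interaction gate stays. Test week 16 only after week 12 in a stated hierarchy, or label it secondary. State the family of comparisons, and quote power for the rule chosen.

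The cost is a sentence or two of analysis text, with no added participants, visits or data. One small downside is that the decisions will no longer match Bonferroni simultaneous confidence intervals.

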### Data management and monitoring

Data gathered by the measurement software will be individually saved to Excel files immediately following the data-gathering process. Assessments of both physical and cognitive ability will initially be recorded on paper forms devised by the research team, which will subsequently be digitized. The hard copies of these forms will be archived for a decade post-study in distinct filing cabinets. These records will ultimately be compiled into a central database table. All information will be maintained within a safeguarded computer system environment. Access to the folders containing the database will be exclusive to the research personnel. Access will be governed by a secure password system. Prior to analysis, a thorough review of the data will be conducted to ensure accuracy before it is input into analytical software. The ethical guidelines of the study include a comprehensive policy on the handling, labeling, and safeguarding of data, in addition to stipulations on its disclosure and collection.

To maintain privacy, data will be stored under a system of pseudonymization, labeled with unique identification numbers for the trial, and held in restricted-access folders that are accessible solely to the trial team. Any documents with personal identifiers, like names, will be kept separately from the main research files. Password protection will secure all databases at the local level, ensuring controlled access to sensitive information.

### Ethical consideration

This study has been approved by the Survey and Behavioral Research Ethics Committee of The Chinese University of Hong Kong (SBRE‐24‐0942). Participants must sign a written informed consent form before participating in the laboratory experiments and complete an electronic informed consent form before taking the online questionnaire.

Furthermore, we have also enlisted a professional fitness trainer to participate in our experimental process, ensuring the professionalism and safety of our entire exercise program design and fitness assessment. All training sessions will be conducted under the guidance and supervision of these trainers, ensuring the safety of participants in each intervention group throughout the exercise process. Participants are instructed to immediately cease activity if they experience any physical discomfort, thereby preventing potential risks and injuries. In case of an adverse event, we have procedures for immediate assessment, first aid provision, and, if necessary, emergency medical services contact. Incident reporting and follow-up care are standard practices.

## Discussion

This randomized controlled trial seeks to explore the potential benefits of physical exercise on esports performance, compare the differential effects of various exercise modalities, and examine the longitudinal sustainability of these effects. With the rapid expansion of the esports industry and its increasing recognition as a legitimate competitive endeavor, there is a need for more empirical evidence to explore supplementary intervention approaches for esports training and performance enhancement, providing a reference for its scientific development akin to traditional sports. By examining the effects of exercise on the gaming skills, psychomotor, and emotional dimensions of esports performance, this RCT protocol aims to address a critical gap in the current understanding of physical interventions for esports competitors.

### Significance of the study

Although previous studies have demonstrated the potential benefits of physical exercise on esports performance [25–28,30,34,35,56], these investigations are often limited by cross-sectional designs [25,67], acute single-bout exercise interventions [26–28,34], or a reliance on indirect metrics of esports performance [26,30]. While a few longitudinal studies targeting esports performance have recently emerged, they are often constrained by short intervention periods and limited sample sizes. Furthermore, they lack the measurement and analysis of sustained effects post-intervention and have yielded inconsistent findings [31,32]. To better understand the role of physical exercise in esports, a more rigorous evaluation of intervention effects is required. This includes assessing whether exercise can yield long-term performance benefits for players and evaluating the longitudinal sustainability of these effects after the intervention ceases. Furthermore, while much of the current research has predominantly utilized HIIT, further optimizing exercise protocols specifically tailored for esports requires head-to-head comparisons of different exercise modalities. Verifying whether alternative exercise modalities are equally effective will also provide valuable, evidence-based options for decision-makers and coaching staff within esports teams. This protocol is specifically designed to provide a comprehensive research framework that addresses these methodological limitations in the existing literature.

The findings of this study aim to provide empirical insights for esports athletes, coaches, and organizations. The connection between physical fitness and cognitive function has been established in traditional sports, but its application to the context of esports remains under-researched. This study has the potential to demonstrate that physical exercise is not only beneficial for general health but also for the specific demands of esports, such as reaction time, strategic thinking, and endurance during prolonged gaming sessions.

By comparing multiple exercise modalities against a control condition, this study seeks to identify more effective physical training parameters for enhancing esports performance. The inclusion of follow-up assessments extends beyond immediate effects to examine the duration of exercise-induced benefits after training cessation—a critical consideration for establishing optimal training frequency that allows esports athletes to balance physical training with technical practice time. Furthermore, the larger sample size enables us to draw more reliable conclusions about the differential effects of HIIT and MICT in FPS players, thereby offering more specific data for exercise prescription.

Moreover, several negative health-related consequences have been traditionally associated with excessive screen time and prolonged sedentary behavior in video gamers [100,101]. Excessive sitting time and screen exposure pose potential risks to the health of esports athletes [102,103]. Studies have linked prolonged screen time with lower levels of physical activity and poor cardiovascular health [104,105]. Except for active video games or virtual sports, the majority of video games are typically played in a sedentary position [106]. Should the results of the proposed trial demonstrate that physical exercise effectively enhances esports performance, they could offer a practical rationale for integrating systematic, structured physical training into standard esports regimens. Consequently, while optimizing their competitive outcomes, esports players would concurrently reap the well-established health benefits of regular exercise. This integration would effectively mitigate the health risks associated with prolonged sedentary behavior, exploring a potential dual benefit of enhanced competitive performance and safeguarded occupational health.

The comprehensive approach of this study may contribute empirical data to the ongoing discussion regarding physical training in competitive gaming. These findings could serve as a reference for esports academies and professional teams seeking to incorporate appropriate physical exercise regimens alongside technical and tactical training. By integrating physical exercise into training models, this approach aims to address health concerns that could otherwise undermine the longevity of players’ careers, thereby supporting more sustainable practices within competitive gaming.

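### The plan tests HIIT against MICT only for a difference, and only after a significant effect, so it cannot show that the two are equally effective and may leave a stated comparison unestimated

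*Protocol article*

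**What the plan says.** The Abstract's objective and the Research objective section both list a comparison of HIIT and MICT among the aims; both are worded as comparisons of effects.

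Under Significance of the study, the article argues that head-to-head comparisons are needed. It continues that "Verifying whether alternative exercise modalities are equally effective" will help decision-makers and coaching staff, and then says the protocol was designed to address the gaps just listed. The same section says "the larger sample size enables us to draw more reliable conclusions about the differential effects of HIIT and MICT".

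Under Data analysis, the longitudinal outcomes are analysed by GEE with a group-by-time interaction. On flicking capacity, "The primary outcome will be tested at a two-sided α level of 0.05". If a main or interaction effect is significant, "post-hoc pairwise comparisons will be performed within the GEE framework using estimated marginal means with a Bonferroni adjustment". The section also promises 95% confidence intervals in general terms. It gives no equivalence or non-inferiority hypothesis, margin or test.

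Under Experimental design, the sample size is set to find a difference: "a minimum sample of 52 participants per group would be required to detect significant effects with 80% power".

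**The concern.** Failing to find a difference is not evidence that there is none. If one intended use of the trial is to tell coaches whether either modality will do, the analysis needs some way to support that statement. A difference test without a margin offers none.

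The conditional step adds a second problem. The HIIT-MICT contrast appears only among the post-hoc comparisons, which depend on a significant effect. If nothing is significant, the plan calls for no estimate of that contrast, although it answers a stated aim. A reader would then have an overall p-value and no interval showing which modality differences remain compatible with the data.

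**Working it through.** **Inputs from the article (Experimental design, Data analysis).** d = 0.4, 80% power, two-sided α = 0.05, 52 evaluable per group, 20% dropout, 65 recruited per group, allocation 1:1:1.

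**Assumptions not in the article.** Baseline-to-week-12 correlation r, shown at 0.5, 0.7 and 0.8; three pairwise contrasts for the Bonferroni step; a single-time-point contrast as an approximation to the GEE contrast.

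**The plan's own figure.** A one-sample or paired t-test with d = 0.4, two-sided 0.05, gives 80.8% power at n = 52 and 79.99% at n = 51, so 52 is reproduced. Then 52 / 0.80 = 65 and 3 × 65 = 195. A two-sample t-test with the same inputs needs 100 per group. That mismatch is a separate matter. Here it matters only because 52 per arm gives limited precision between arms.

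**Precision of HIIT minus MICT, in SD units.**
- No gain from baseline: SE = √(2/52) = 0.196. The 95% half-width is 1.96 × 0.196 = 0.384.
- Bonferroni for three pairs (z = 2.394): 2.394 × 0.196 = 0.469.
- All 65 per arm retained: 1.96 × √(2/65) = 0.344.
- Baseline-adjusted: SE = √(2/52 × (1 − r²)).
- Change score: SE = √(2/52 × 2(1 − r)). The half-widths are 0.384, 0.298 and 0.243 at r = 0.5, 0.7 and 0.8.

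**Chance of a non-significant contrast at 52 per arm** (noncentral t; Bonferroni-adjusted figure in brackets):

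| Setting | 95% half-width | True difference 0.2 SD | True difference 0.4 SD |
|---|---|---|---|
| No gain from baseline | 0.384 (0.469) | 83% (92%) | 48% (65%) |
| Baseline-adjusted, r = 0.5 | 0.333 (0.407) | 78% (89%) | 35% (53%) |
| Baseline-adjusted, r = 0.7 | 0.275 (0.335) | 71% (84%) | 19% (34%) |
| Baseline-adjusted, r = 0.8 | 0.231 (0.282) | 61% (76%) | 8% (17%) |

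A difference of 0.2 SD, half the planning effect, is more likely missed than found in every row. For 0.4 SD the answer turns on r.

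**Could equivalence be shown if it were wanted?** Take two one-sided tests at 0.05, a true difference of zero and margin m. Power = 2Φ(m/SE − 1.645) − 1, set to 0 if negative. The margins are assumptions.
- m = 0.4 SD: 31%, 52%, 77% and 92% for r = 0, 0.5, 0.7 and 0.8.
- m = 0.3 SD: 0%, 10%, 38% and 63%.
- m = 0.2 SD: 0% up to r = 0.7, and 4% at r = 0.8.

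**The case against.** The strongest reply is that the trial never sets out to prove equality. The phrase about equal effectiveness is rationale in the Discussion, not an objective, hypothesis or decision rule, and its wording leaves the answer open. The objectives ask how the effects compare, which a difference test fits, and a trial without an equivalence hypothesis needs no margin. The article also promises 95% confidence intervals.

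Most of this stands. A reader might infer that the investigators intend to read a non-significant HIIT-MICT result as equal effectiveness. The article does not say so. A reader might also infer that the trial is too imprecise for any equivalence statement. That does not follow: the width depends on a correlation the article does not give, and with r of 0.7 to 0.8 a margin of 0.4 SD would give 77% to 92% power. Likewise, the 48% and 65% miss rates at 0.4 SD apply only without gain from baseline.

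Two things remain. The Discussion ties the equal-effectiveness question to what this protocol was designed to address, and nothing in the analysis can answer it. And the general promise of intervals does not ensure that the HIIT-MICT interval is produced, because that contrast sits behind a significance condition. Read literally, a main effect of time alone would meet the condition, so omission is possible rather than certain.

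**Conclusion.** The point holds as a mismatch between one stated use of the trial and its analysis. The plan can detect a HIIT-MICT difference. It cannot establish equal effectiveness, and it does not guarantee an estimate of a comparison named in the objectives. The firm part is the missing margin and the conditional contrast; neither depends on the arithmetic.

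The size is less firm. At 52 per arm the half-width is 0.38 SD without gain from baseline (0.47 SD with three-way Bonferroni) and about 0.33 to 0.23 SD with baseline adjustment for assumed r of 0.5 to 0.8. A difference of 0.2 SD would usually be missed. The article does not say that 0.2 SD is important; it serves here as half the planning effect. At the Bonferroni level, the chance of missing 0.4 SD runs from 65% with no gain to 17% at r = 0.8 with baseline adjustment.

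**What to change.** 1. In Data analysis, state that the week-12 HIIT-MICT contrast on flicking capacity will be reported as an estimate with its 95% confidence interval whatever the overall test shows.
2. State that a non-significant contrast will not be read as equal effectiveness, and that the interval will guide interpretation.
3. In Significance of the study, replace the equal-effectiveness wording with a comparison of effects.
4. Only if the investigators want to claim equal effectiveness: fix and justify a margin before results are known, and say which interval must lie inside it. A 90% interval corresponds to two one-sided tests at 0.05; a 95% interval is stricter.

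Items 1 to 3 change analysis text and wording only, with no new data or participants. The downside is that the modality comparison may have to be reported as inconclusive. Item 4 is optional; depending on the margin and the correlation, it may call for a larger sample. With no gain from baseline, 80% power needs 108 per arm for a margin of 0.4 SD and 429 for 0.2 SD.
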